## Introduction

### Background

Chronic fatigue syndrome, also known as myalgic encephalomyelitis (CFS/ME), is a condition characterized by chronic disabling fatigue, which is not better explained by an alternative diagnosis [1-3]. The prevalence of CFS/ME in the population is between 0.4 and 2.5% [3-5]. A working group, reporting to the Chief Medical Officer for England, concluded the following: "CFS/ME is a relatively common clinical condition, which can cause profound, often prolonged, illness and disability, and can have a substantial impact on the individual and the family" [4]. The prognosis is poor with a median of 7% recovering without treatment [6].

The National Institute for Health and Clinical Excellence (NICE) guidelines recommend that patients with CFS/ME are offered GET (or cognitive behavior therapy [CBT]) [7]. In support of this guidance, two systematic reviews showed no harm to patients from GET [8,9]; however, it was concluded that larger trials should be completed to confirm the recommendations. The PACE trial (pacing, graded activity, and cognitive behavior therapy: a randomized evaluation) is the largest ever trial testing GET and CBT for CFS with 641 secondary care patients recruited [10]. Specialist medical care (SMC) alone was compared with SMC plus one of three therapies (adaptive pacing therapy, CBT, or GET). GET was found to be an effective and safe treatment, with 82% being satisfied with GET [11]. In contrast to this research, surveys of ME charity members have suggested that GET is perceived as a harmful and unacceptable treatment. In a recent survey, 56% of those who had received GET reported feeling “worse” afterwards, with 53% reporting GET to be unacceptable [12]. Specialist therapist-delivered GET is also intensive and expensive, with up to 15 sessions required over a 3 to 6-month period [9,11], and United Kingdom (UK) National Health Service (NHS) access is often poor and with long waiting lists [13]. An effective and safe guided self-help GET approach would be helpful to all involved.

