The main secondary outcome measure will be the validated self-rated CGI score, which we will use to measure both change in “CFS” and change in “general health” at the end of treatment, compared with baseline. Each will have 7 possible scores from "very much worse" (score of 7) to "very much better" (score of 1)[39]. Both safety and efficacy can be recorded with this item; we will count scores of 1 and 2 (“very much” and “much” better) as positive outcomes, and scores of 6 and 7 (“very much” and “much” worse) as negative outcomes. Scores of 3-5 (“a little” better, no change, and “a little” worse) will be regarded as no change.

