#### Missing Data

Item-level missing data on the primary and secondary outcome variables at baseline and follow-up will be imputed using mean replacement (prorating). Prorating will be implemented only when less than 20% of item responses per scale are missing. The reasons for missing baseline and follow-up whole-scale data will be summarized using the CONSORT diagram. We will identify baseline characteristics associated with missing data to allow us to impute data to do sensitivity analyses.

#### Analysis for Hypothesis 1

Our primary intention-to-treat analysis will compare the SF-36 PF and CFQ at 12 weeks between groups adjusted using multivariable linear regression analyses [45]. Intention-to-treat (ITT) analyses will be conducted on data from all randomized participants with information at follow-up (ie, modified ITT) regardless of any departure from the allocated treatment arm. We will adjust for our stratification factors (depression, center, and severity of disability) as well as baseline values of outcomes and treatment arm.

A secondary analysis will explore the association between treatment arm and having achieved a clinically useful improvement on the SF-36 PF (ie, an 8-point increase) and the CFQ (ie, a 3-point decrease) using chi-squared analysis.

Analysis of the secondary outcome, the CGI, will compare the proportions scoring “much” or “very much” better (1 and 2), the proportions scoring “a little better,” “no change,” or “a little worse” (3 to 5), and the proportions scoring “much” or “very much” worse (6 and 7) across treatment arms, using an ordinal logistic regression adjusting for our stratification variables.

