#### Sensitivity Analysis

Sensitivity analysis will be conducted to assess the impact of missing data on our results. We will estimate whole-scale missing data due to loss to follow-up using multiple imputation by chained equation. This will allow us to conduct a strict ITT for all respondents who took part at baseline. Following recent guidelines, we will also conduct a sensitivity analysis that will take into account the partially nested design of the study and, therefore, assess the potential impact of the “therapist effect” on our results [46]. Further analysis will be conducted to adjust for potential confounders, including sex and age.

A per-protocol analysis will serve as a further sensitivity analysis to investigate the robustness of the conclusions of the primary analysis, following departures from the randomized intervention policies. This will exclude those participants in the control arm who used a GET self-help approach. Subgroup analyses including only those meeting the Oxford or CDC criteria for CFS will also be undertaken. We will analyze moderators of improvement, such as these criteria, but also depression and severity of physical function and fatigue. These subgroup analyses are exploratory and will be interpreted with due caution [47].

#### Analysis for Hypotheses 2 and 3

Chi square will be used to describe any difference in satisfaction (ie, satisfied vs nonsatisfied) across treatment arms and any differences in SAEs, SARs, or serious deterioration (1+ vs none) across treatment arms.

The above plan is what we intend to do; however, the final analyses reported may differ from those planned, allowing for *post hoc* analysis where it is indicated [48]. We will report alternative methods if statistical models do not converge, and omit planned analyses that are superseded, redundant, or no longer of interest. We will report any changes in consequent papers.

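### One ordinal odds ratio for the three-group CGI cannot report benefit and harm separately, although the protocol intends the item to show both

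*Protocol article*

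**What the plan says.** All references are to the protocol article; no SAP is at hand.

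- **Role.** Under Primary Outcomes: "The main secondary outcome measure will be the validated self-rated CGI score". It is asked twice, for CFS and for general health.
- **Scale and grouping.** The same section says "Each will have 7 possible scores from" very much worse (7) to very much better (1). Scores 1-2 count as positive and 6-7 as negative; scores 3-5 "will be regarded as no change".
- **Purpose.** "Both safety and efficacy can be recorded with this item".
- **Model.** Analysis for Hypothesis 1 compares the three proportions "across treatment arms, using an ordinal logistic regression adjusting for our stratification variables". It states no proportional-odds check, no alternative model and no separate contrast for either end.
- **Where else CGI 6-7 is used.** Safety Measures and Reporting counts it as one component of serious deterioration, beside withdrawal due to worsening and a fall of 10 or more on the SF-36 PF. Analysis for Hypotheses 2 and 3 applies a chi-square test to "any differences in SAEs, SARs, or serious deterioration (1+ vs none) across treatment arms".
- **Description.** Descriptive Statistics for Primary and Secondary Outcomes promises number and percentage for discrete outcomes, by group.

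**The concern.** A single common odds ratio summarises a net shift along the scale. It answers the efficacy question well if the intervention moves the distribution one way. It cannot also answer the safety question, because movement into the top group and movement into the bottom group enter it with opposite signs.

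The protocol treats movement in both directions as possible. Its Background sets a large trial that found GET effective and safe against a survey of charity members in which "56% of those who had received GET reported feeling" worse. The qualitative study is justified by variation in patients' responses, and it samples GES participants from both CGI extremes.

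At stake is the reading of the main secondary outcome. A reported odds ratio near 1 could be taken as no effect when more participants in the GES arm were much better and more were much worse.

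**Working it through.** **The plan's own figure.** The document gives a sample size for the SF-36 PF and none for the CGI. With difference 8, SD 18, alpha 2.5% (two-sided assumed) and 80% power:

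n per arm = 2 × 18² × (2.241 + 0.842)² / 8² = 648 × 9.505 / 64 = 96.2, so 97 by the normal approximation and 98 by the t distribution. Allowing 10% loss, 98/0.9 = 109 per arm, 218 in total. This reproduces, and 98 per arm is used below. No alpha is stated for the CGI; 0.05 two-sided is assumed.

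**Illustrative table (assumed counts, better/middle/worse).** SMC 10/78/10; GES 20/58/20.

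- Odds ratio at the upper cut (1-2 versus the rest): (20/78)/(10/88) = 2.26.
- Odds ratio at the lower cut (1-5 versus 6-7): (78/20)/(88/10) = 0.44.
- The two are reciprocals, so the common odds ratio is 1.00, p=1.00.
- 2-df chi-square, expected counts 15/68/15 per arm: 4 × 25/15 + 2 × 100/68 = 6.67 + 2.94 = 9.61, p=0.008.
- Either tail as a binary contrast: 20/98 − 10/98 = 10.2 percentage points. SE = √(0.204×0.796/98 + 0.102×0.898/98) = 0.0509, so the 95% CI is 0.2 to 20.2 points (unadjusted).

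**Is exact symmetry needed?** Rejection rates come from 20,000 simulated trials, unadjusted for strata, using the tie-corrected Wilcoxon test (the score test of the proportional-odds model). Odds ratios and their p-values are from expected counts. All distributions are assumed, in per cent; an odds ratio above 1 favours GES.

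| SMC | GES | Common OR (p) | Ordinal test rejects | 2-df chi-square rejects |
|---|---|---|---|---|
| 10/80/10 | 20/60/20 | 1.00 (1.0) | 5.6% | 79% |
| 5/85/10 | 20/60/20 | 1.22 (0.53) | 10% | 97% |
| 5/85/10 | 20/65/15 | 1.59 (0.16) | 29% | 92% |
| 5/85/10 | 20/75/5 | 3.41 (0.001) | 90% | 88% |

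The ordinal model does well in the last row, where the shift runs one way. It does poorly in the first three, where both tails grow.

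**How far the serious-deterioration test covers harm.** For CGI 6-7 alone rising from 10% to 20%, 98 per arm, simulated power is about 51%. The composite adds other components. If these independently add 10% in both arms (assumed), the rates become 0.10 + 0.90×0.10 = 19% and 0.20 + 0.80×0.10 = 28%, and power is about 32%. If they add 30%, the rates become 37% and 44%, and power is about 17%. Overlap between components would soften this.

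**Would keeping seven levels cure it?** No. In an assumed symmetric help-and-harm case on seven levels, the ordinal test rejects 5.7% of the time.

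**The case against.** **Harm is examined elsewhere.** CGI 6-7 feeds the serious-deterioration chi-square, and the percentages by arm will be shown. This stands in part. A reader might infer that harm would be hidden altogether; the document does not support that, since a doubling of both tails would be visible in the table. But the composite mixes in withdrawals and SF-36 PF falls. Its definition also varies: Safety Measures and Reporting counts withdrawal due to worsening, while 12-Week Follow-Up counts active withdrawal without that condition. No matching test exists for scores 1-2.

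**The model is over-read.** The text says ordinal logistic regression, not proportional odds, and assumption checks commonly belong in an SAP. This is fair as to checks, and their absence is not the point made here. The choice of one ordinal model for an item meant to show two things is stated in the protocol. The provision for alternative methods concerns models that fail to converge, and this one would converge, to an odds ratio near 1. Nor does proportional odds assume that every participant moves the same way; it assumes only a common odds ratio across the cut-points.

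**The cut from seven levels to three.** A reader might infer that this is an error that discards a known, large share of the information. The document does not support that. The grouping is a pre-specified threshold for a meaningful change and is applied consistently, and no CGI distribution is given. Under proportional odds, information is proportional to 1 − Σp³. If the seven levels are used evenly, the ratio of three to seven levels is 0.875/0.980 = 0.89, a loss of 11%. With 3/10/22/35/18/9/3 per cent, it is 0.574/0.939 = 0.61, a loss of 39%. With an assumed 6/87/7 split, it is 0.341/0.909 = 0.37, a loss of 63%. The loss is a trade-off of unknown size.

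**The scenario is extreme.** Exact cancellation does need symmetry, and the survey cited in the Background has no comparator. But the asymmetric rows above lose most of the power too.

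**Conclusion.** The concern holds for the mismatch between purpose and model: the CGI is meant to show efficacy and safety, and the only analysis of the item as such yields, in its standard form, one odds ratio that can be near 1 when both outer groups grow. In the illustrative table it is 1.00 (p=1.00) against p=0.008 for a 2-df chi-square. The existing safety comparison and descriptive percentages reduce the risk of missing harm but do not remove it, and benefit at scores 1-2 has no test of its own.

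This rests on assumed CGI distributions, a standard proportional-odds fit and a two-sided 0.05 level. It does not show that GES acts in both directions. It concerns a secondary outcome and its safety reading only.

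**What to change.** In Analysis for Hypothesis 1, for each CGI item (CFS and general health), replace or supplement the single ordinal odds ratio with two binary contrasts adjusted for the stratification variables:

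- scores 1-2 versus the rest (benefit);
- scores 6-7 versus the rest (harm);

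each reported as a risk difference with a 95% CI. Supplementing is reasonable, because the ordinal model remains efficient for a one-way shift. The three-group table stays as description. A seven-level ordinal model is at most an optional sensitivity analysis: its gain depends on the unknown distribution, and it does not address cancellation.

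**Cost.** Two contrasts on two items make four models, so six in place of two if the ordinal models are kept. There is some added multiplicity among secondary analyses, which should be acknowledged. Counts at 6-7 may be sparse, so a simpler or unadjusted interval should be named as the fallback. The cut-points are the protocol's own, and no new data or sample-size change is needed. The article reports that recruitment has ended and analysis is underway, so the change should be dated and reported as a departure from the plan, as the article already undertakes to do for any changes.

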### Randomization

The recruiting researcher will log in to the Web-based automated randomization service/system operated by the UK Clinical Research Collaboration (UKCRC) registered King’s Clinical Trials Unit at the Institute of Psychiatry, King’s College London for the intervention allocation, which will be conveyed to the participant by the recruiting researcher. Allocation will be at the level of the individual, using block randomization with randomly varying block sizes, to preserve allocation concealment. Randomization will be stratified by (1) depression (Hospital Anxiety and Depression Scale; cut-off = 11); (2) severity of disability (SF-36 physical functioning subscale ≤40 and ≥45, which was close to the mean score from all participants in the PACE trial [11]; and (3) by center. This will help to ensure equal proportions of depressed and more severely disabled participants in each treatment arm. Automatic emails will confirm the intervention allocation. If for any reason the randomization service is unobtainable, randomization will be completed during the next working day and the participant will be told of the result by telephone.

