#### Baseline

The following self-rated inventories will be collected at the first assessment (baseline): 11-item Chalder fatigue questionnaire (CFQ), using Likert scoring [30]; SF-36 physical function short form subscale (SF-36 PF) [31]; Hospital Anxiety and Depression Scale (HADS) [32]; Euroqol Questionnaire (EQ-5D) [33]; Work and Social Adjustment Scale (WSAS) [34]; International Physical Activity Questionnaire (IPAQ) [35]; Tampa Scale of Kinesiophobia-Fatigue (TSK-F) [36]; Client Service Receipt Inventory (CSRI) [37]; and Patient Health Questionnaire (PHQ-15) [38]. Participants will be asked when their CFS/ME started; whether they have ever received GET, CBT, or pacing from a therapist; whether they have ever used any listed self-help resources; and whether they are members of a CFS/ME self-help group. Participants will also be asked about their ethnicity, highest education level, current employment status, whether they have had to reduce/stop work due to their CFS/ME, other health problems, and whether they are taking antidepressant medication for any reason.

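### The CGI model is valid but omits baseline fatigue and uses SF-36 PF and HADS only as dichotomies; adding the continuous baseline scores could raise power modestly at little cost

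*Protocol article*

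**What the plan says.** Under Primary Outcomes the article states: "The main secondary outcome measure will be the validated self-rated CGI score". The CGI is rated "at the end of treatment, compared with baseline", so it is a change rating with no baseline value of its own. Scores 1–2 count as a positive outcome, 3–5 as no change and 6–7 as a negative outcome.

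Under Analysis for Hypothesis 1 these three categories are compared between arms "using an ordinal logistic regression adjusting for our stratification variables". The Randomization section defines the stratification variables as "depression (Hospital Anxiety and Depression Scale; cut-off = 11"), "severity of disability (SF-36 physical functioning subscale ≤40 and ≥45"), and center. Fatigue is not among them.

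For the two primary outcomes the same analysis section goes further: "We will adjust for our stratification factors (depression, center, and severity of disability) as well as baseline values of outcomes and treatment arm".

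The Baseline section lists the scores collected before treatment, beginning with "11-item Chalder fatigue questionnaire (CFQ), using Likert scoring [30]; SF-36 physical function short form subscale (SF-36 PF) [31]; Hospital Anxiety and Depression Scale (HADS"). The Sensitivity Analysis section plans further adjustment for possible confounders, naming sex and age. It also lists depression and the severity of physical function and fatigue as possible moderators of improvement.

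**The concern.** The article fixes the covariate set for the CGI, so this is a stated choice and not a detail left to another document. Three features make the choice look weaker than it need be.

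- Baseline fatigue is controlled neither by the stratified randomization nor by the CGI model, although one of the two CGI ratings concerns CFS itself.
- SF-36 PF enters as one cut. The Primary Outcomes section reports that an appreciable minority entered with near-normal physical function. The upper stratum pools them with people scoring 45, so the factor hides the spread that led to the second primary outcome.
- The authors treat depression, physical function and fatigue as possibly relevant to response, since they plan moderator analyses on them.

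That the CGI rates change does not make baseline severity uninformative about it. At stake is some power for the main secondary outcome, which carries both benefit and worsening, and exposure to chance imbalance in baseline fatigue.

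**Working it through.** **Sample size used.** The article gives no power figure for the CGI, so its SF-36 PF calculation sets the number analysed. With difference 8, SD 18, two-sided alpha 2.5% and power 80%:

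n per group = 2 × (2.241 + 0.842)² × (18/8)² = 2 × 9.505 × 5.0625 = 96.2, i.e. 97. The t-based version gives 97.5, i.e. 98. Then 98/0.9 = 108.9, i.e. 109 per group and 218 in total.

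The stated figures reproduce. The check below uses 98 per arm (196 analysed).

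**How much prognostic information is left out.** Suppose three independent normal scores each explain R²/3 of the latent CGI. A median split keeps 2/π = 64% of what its score explains. Two scores are split and one is omitted, so the share left out is (R²/3) × [1 + 2 × (1 − 0.637)] = (R²/3) × 1.727. That is 8.6% of variance at R² = 15% and 17.3% at R² = 30%.

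**Effect on power.** Proportional-odds models were simulated with 1,500 trials per scenario and a two-sided 5% test.

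- Model A: arm, center and the two dichotomies.
- Model B: model A plus continuous CFQ, SF-36 PF and HADS.

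Assumptions not in the article: control-arm split 10/80/10 or 20/60/20; conditional odds ratio 2.0 or 2.5; independent scores; cuts at the median; equal arms without balancing on the strata. Power (%), A → B:

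| R² | 10/80/10, OR 2.0 | 10/80/10, OR 2.5 | 20/60/20, OR 2.0 | 20/60/20, OR 2.5 | Change (points) |
|---|---|---|---|---|---|
| 0% | 50.2 → 50.5 | 74.3 → 73.7 | 70.5 → 70.3 | 90.4 → 90.2 | -0.6 to +0.3 |
| 3% | 47.5 → 49.1 | 73.8 → 73.1 | 67.7 → 68.6 | 88.9 → 89.6 | -0.7 to +1.6 |
| 9% | 45.8 → 47.4 | 74.3 → 75.8 | 66.1 → 67.9 | 88.1 → 89.4 | +1.3 to +1.8 |
| 15% | 48.2 → 50.5 | 70.4 → 73.6 | 60.3 → 63.9 | 85.7 → 88.6 | +2.3 to +3.6 |
| 30% | 42.1 → 48.5 | 64.1 → 68.8 | 54.7 → 64.8 | 81.1 → 88.6 | +4.7 to +10.1 |

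Simulation error on each power figure is about 1 point.

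**Where the gain comes from.** For 20/60/20 and OR 2.0 at R² = 15%, the mean log-odds ratio goes from 0.660 to 0.708 and its mean standard error from 0.293 to 0.301. The ratio rises from 2.25 to 2.35. At R² = 30% the figures are 0.626 to 0.731 and 0.295 to 0.312, a ratio of 2.12 to 2.34. The standard error rose in every scenario; the estimate moved further from zero.

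**Cross-check.** A second set-up used two independent scores, each correlated r with the latent outcome, one split at the median and one omitted (latent shift 0.42 SD, 3,000 trials). Gains were about 0 to 2 points at r = 0.2, 4 to 5 at r = 0.3 and 7 to 8 at r = 0.4. Joint R² = 2r² is 8%, 18% and 32%, so the pattern agrees.

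**Chance imbalance in CFQ.** With 98 per arm, the difference in baseline means has standard error √(2/98) = 0.143 SD, so the 95% range is ±0.28 SD. If CFQ alone explains 5% of a latent variable with total variance 3.29/0.85 = 3.87, its slope is √(0.05 × 3.87) = 0.44 per SD. An imbalance at the edge of that range shifts the log-odds by 0.28 × 0.44 = 0.12, against 0.69 for an odds ratio of 2.0. At 10% (total variance 3.29/0.70 = 4.70) the slope is 0.69 and the shift 0.19.

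**The case against.** The strongest reply is that nothing here is wrong. Adjusting for the stratification factors matches the design and gives a valid test, whose error rate already allows for chance imbalance. That stands.

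A reader might infer that the plan throws away precision at no cost to anyone. The calculation does not support this. In a logistic model, prognostic covariates raise the standard error of the log-odds ratio slightly; what may improve is power. The change is also not free, because the odds ratio becomes conditional on more covariates.

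A reader might also infer that the CGI model is inconsistent with the primary models. It is not: the baseline term used there has no direct counterpart for a rating of change.

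The size of the gain is assumed. No correlation between baseline scores and CGI is given, and independent scores are a favorable assumption, since overlapping scores would jointly explain less. The planned further adjustment for confounders is open-ended, although it does not name CFQ.

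Finally, a reader might extend the point to the primary CFQ regression. That model already includes baseline CFQ, its baseline term may already cover both outcomes, and nothing here sizes any gain. The point is confined to the CGI.

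What survives is that the scores are already collected, the change is small, and neither set-up showed a power loss beyond simulation noise.

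**Conclusion.** The point holds as a low-severity, optional improvement to a valid model. As stated, the CGI analysis leaves out baseline fatigue and reduces SF-36 PF and HADS depression to two levels. Using the continuous scores would reduce the analysis's exposure to chance imbalance in fatigue and could raise power. The size depends wholly on how well the scores predict a change rating: negligible when they predict weakly, and material only when they explain about 30% of the latent outcome. The result also rests on proportional odds, the assumed category splits and odds ratios, and about 98 analysed per arm.

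**What to change.** Under Analysis for Hypothesis 1, state that the CGI ordinal logistic model adjusts for center, the depression and disability strata, and the continuous baseline CFQ, SF-36 PF and HADS depression scores.

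The cost is one line of text and three parameters (seven slopes instead of four). With a 10/80/10 split, each outer category would hold about 0.10 × 98 = 10 control participants, so sparseness should be considered when the model is fixed. The report should say that the odds ratio is conditional on the longer covariate list.

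Timing matters. The Results section says analysis is under way, and Blinding to Outcome Measures keeps the statistician masked until the main analysis is complete. If masking still holds, fix the change now and record it. If not, keep the stated model as the planned CGI analysis and report the extended one as a labelled supportive analysis. Either route fits the article's commitment to report changes.
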